### Missing data analysis

In this analysis, the purpose to treat concept (ITT) will be applied. Thus, when respondents’ final results are compared to their initially allocated party, regardless of care allocation, loss to follow up, or violation of the original protocol, they intend to treat the study. As a result, all missing data will be examined in this analysis, as the ITT concept can only be implemented when all respondents’ data is available.

The ability to perform ITT will be jeopardized if data is missing, and its conclusions will be undermined. Before the start of the research, strategies for dealing with missing data were devised. The amount of missing data explored, the trends involved, and variables associated with missingness would be the methods of approaching them. First, determine the sensitivity of the data. The primary analysis will be performed using the multiple imputation process, followed by sensitivity analysis. The aim to treat definition (ITT) will be used in this research. Intention to treat studies compares respondents’ final results to their initially assigned party, regardless of treatment allocation, follow-up loss, or the original protocol’s violation.

As a result, all missing data will be analyzed as part of this study since the ITT definition can only be applied if all respondents’ data is available. If data is lacking, the ability to execute ITT will be jeopardized, and the conclusions drawn from it will be undermined as well. Strategies for coping with missing data were formulated before the start of the study. The methods for approaching them would be investigating the amount of missing data, the patterns involved, and the variables associated with missingness. The primary analysis will be done with multiple imputations, and then a sensitivity analysis will be done to see how stable the conclusions are with and without missing data. Conclusions’ robustness when missing data is present and when it is not.

### Analysis of baseline variables

This analysis is being carried out to address the study’s first objective. The data will first be tested for normality using graphical and statistical techniques. The main objectives of analyzing baseline variables are to demonstrate comparability of respondents’ characteristics between treatment groups, to provide for covariate-adjusted analysis, which refines the overall treatment effect by taking into account baseline characteristics that are correlated to the outcome, and to set the context for subgroup analysis, which examines treatment differences on a more detailed level (Pocock et al., 2002). The chi-square test will be used for categorical data, while the independent T-test or Mann-Whitney U test will be used for continuous data.

### Generalized estimating equation (GEE)

The data from the sample will be calculated longitudinally to address the second and third hypotheses (in repeated measures). Comparing the variations in results between and within treatment groups over time points when adjusting for covariates, the Generalized Estimating Equation (GEE) will be used.

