**Method:**

A single-blind cluster randomized controlled trial will conduct at six districts in Selangor. Randomly selected respondents who fulfilled the inclusion criteria will be invited to participate in the study. Health education module based on Health Believed Theory will be delivered via health talks and videos coordinated by liaison officers. Data at three-time points at baseline, immediate, and 3 months post-intervention will be collected. A validated questionnaire will assess participants’ background characteristics, knowledge, skill, and preparedness on disaster preparedness and perception towards disaster. Descriptive and inferential statistics will be applied for data analysis using IBM Statistical Package for Social Sciences version 25. Longitudinal correlated data on knowledge, skills, preparedness, and perception score at baseline, immediate post-intervention, and 6 months post-intervention will be analyzed using Generalized Estimating Equations (GEE).

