### Sample size estimation

The sample size (N) for this study was calculated by comparing the populations of two groups when the endpoint is quantitative. Using the formula by Lameshow and Lwanga (1990):
$$ N=\frac{{\left[{\mathrm{Z}}_{1-\sigma /2}\surd 2\mathrm{P}\left(1-\mathrm{P}\right)+{\mathrm{Z}}_{1-\beta}\surd {\mathrm{P}}_1\left(1-\mathrm{P}\right)+{\mathrm{P}}_2\left(1-{\mathrm{P}}_2\right)\right]}^2}{{\left({P}_1-{P}_2\right)}^2} $$

Where,

N = Sample size estimation

Z_1− σ/2_ = Standard error associated with 95% confidence interval 1.96

Z_1− β_ = Standard error associated with 80% power = 0.842

P_1 =_ Population proportion 1

P_2_ = Population proportion 2

P = P_1 +_ P_2_ / 2

Thus, the calculation below is based on study flood preparedness [9]:

The proportion of follow-up for flood preparedness in the intervention group.

P_1_ = 79.6% = 0.79.

Proportion of follow-up for flood preparedness in control group.
$$ {\mathrm{P}}_2=40.2\%=0.40 $$$$ \mathrm{P}={\mathrm{P}}_{1+}{\mathrm{P}}_{2/}2=\left(0.79+0.40\right)/2=0.59 $$$$ N=\frac{{\left[1.96\surd 2(0.59)\left(1-0.59\right)+0.84\surd 0.79\left(1-0.79\right)+0.40\left(1-0.40\right)\right]}^2}{{\left(0.79-0.40\right)}^2} $$$$ N=3.53/0.15 $$$$ N=24 $$

Taking into account comparison 2 groups.
$$ N=48 $$

Taking into account the design effect = 48 x [1 + (m-1) ICC].

Where m = average cluster size, ICC = intracluster correlation coefficient.

m = 31 [10], ICC = 0.005 based on adjusted ICC for individual- and cluster-level characteristics [10].

Thus, 48 × [1 + (31 – 1)0.005] = 55.2

Adjusting 34% attrition rate [11].

55.2 / 0.66 = 84 final sample sizes estimated for both intervention and control group.

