## Data analysis

### Data entry and analysis

Respondents’ responses to distributed questions will be used to enter data. The research assistant will document the response into IBM SPSS Version 25 (Statistical Package for Social Sciences). Before the final review, data cleaning will be performed to look for any missing data or outliers. Then, the data will be translated to long-form for analysis using the Generalized Estimating Equation (GEE). Descriptive and inferential statistics will be used to analyze the data. In descriptive statistics, continuous data will be reported in either a mean with standard deviations or a median with an interquartile range. Categorical data will be represented in percentages, while continuous data will be reported in either a mean with standard deviations or a median with an interquartile range. The histogram, skewness over the standard error of skewness, and statistical tests of Kolmogorov-Smirnov and Shapiro-Wilk normality tests will be used to screen for normality. If the normality test conditions are met, parametric tests will be used to continue the analysis; otherwise, non-parametric equivalents will be used. A significant alpha level of 0.05 will be used for inferential analysis, and *P*-values will be stated as two-sided.

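### The GEE takes the baseline score as one of three responses; read naturally as a comparison of change, it is less precise than adjusting for baseline and does not match the follow-up comparison behind the sample size

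*Protocol article*

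**What the plan says.** Three places in the protocol article bear on this.

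- **Abstract, Method:** "Longitudinal correlated data on knowledge, skills, preparedness, and perception score at baseline, immediate post-intervention, and 6 months post-intervention will be analyzed using Generalized Estimating Equations". The baseline score is thus listed with the two later scores as data that the GEE models.
- **Generalized estimating equation (GEE):** "Comparing the variations in results between and within treatment groups over time points when adjusting for covariates, the Generalized Estimating Equation (GEE) will be used". No arm-by-time term, contrast or covariate list is given, and nothing is said on whether the arms share a common mean at baseline.
- **Sample size estimation:** "The sample size (N) for this study was calculated by comparing the populations of two groups when the endpoint is quantitative". The formula that follows is nevertheless the one for two independent proportions. Its inputs are one follow-up proportion per arm, 79.6% (used as 0.79) and 40.2% (used as 0.40); the second is labelled "Proportion of follow-up for flood preparedness in control group". It has no baseline term, no repeated measurement and no within-person correlation.

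Two further sections matter. Missing data analysis makes multiple imputation primary. Analysis of baseline variables provides for covariate adjustment but does not say that the T0 outcome score is a covariate.

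**The concern.** If T0 is a response and each arm has its own mean at each visit, the between-arm comparison over time is the difference in mean change. It subtracts the whole observed baseline difference, noise included. With about 24 effective respondents per arm and short scores (0 to 9 and 0 to 10), chance baseline differences can be sizeable.

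Two things follow. First, precision is given away: the T0 score is already planned for every respondent, and using it as a covariate always does better than subtracting it. Second, the sample size describes another comparison, so a reader cannot tell what the 80% applies to. At low rho a change contrast would be less precise than ignoring baseline altogether.

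**Working it through.** **Inputs from the documents.** Alpha: "A significant alpha level of 0.05 will be used for inferential analysis", with P-values that "will be stated as two-sided". Sample size: "Standard error associated with 95% confidence interval 1.96" and "Standard error associated with 80% power = 0.842"; P1 = 0.79, P2 = 0.40; m = 31; ICC = 0.005; attrition 34%.

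**Assumed.** rho, the correlation between a respondent's T0 score and follow-up score, shown from 0 to 0.6; equal variances over time; for contrasts that use both follow-ups, the same correlation between every pair of visits and the same effect at both.

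**Step 1. Reproduce the plan's figure.**
[1.96 x sqrt(2 x 0.595 x 0.405) + 0.842 x sqrt(0.79 x 0.21 + 0.40 x 0.60)]^2 / 0.39^2 = 23.7, so 24 per arm and 48 in all. 48 x 1.15 = 55.2, and 55.2 / 0.66 = 83.6, so 84. The figure reproduces, and it is a single-time-point calculation.

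**Step 2. What the GEE would estimate.** On the score scale, with an arm-by-visit mean model and complete data (each imputed dataset is complete), the GEE returns the arm-by-visit means whatever the working correlation. The arm-by-time contrast is then the difference in mean change. Variance relative to a comparison at one follow-up:

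- change to one follow-up: 2(1 - rho)
- mean of two follow-ups minus baseline: (1 + rho)/2 + 1 - 2 rho = 1.5(1 - rho)
- one follow-up with T0 as covariate, or arms constrained equal at T0: 1 - rho^2

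For one follow-up, adjusted over change is (1 - rho^2) / [2(1 - rho)] = (1 + rho)/2. This is 0.60 at rho 0.2, 0.75 at 0.5 and 0.80 at 0.6, and below 1 for every rho below 1.

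**Step 3. Power.** Invert the plan's own formula with effective n per arm = 84 x 0.66 / 1.15 / 2 = 24.1, divided by the variance factor f:

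power = Phi{[0.39 x sqrt(24.1/f) - 1.96 x sqrt(2 x 0.595 x 0.405)] / sqrt(0.79 x 0.21 + 0.40 x 0.60)}

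The joint 2-df group-by-time test uses a noncentral chi-square with noncentrality 7.85 / [1.5(1 - rho)], where 7.85 = (1.960 + 0.842)^2. The total N column is 84 x 2(1 - rho), rounded up.

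| rho | Change, one follow-up | Total N to restore the planned power | Joint test | Averaged follow-ups | T0 as covariate, one follow-up |
|---|---|---|---|---|---|
| 0 | 49.6% | 168 | 52.3% | 62.5% | 80.8% |
| 0.2 | 59.5% | 135 | 62.4% | 72.8% | 82.4% |
| 0.3 | 65.7% | 118 | 68.6% | 78.7% | 84.5% |
| 0.4 | 72.8% | 101 | 75.7% | 84.9% | 87.4% |
| 0.5 | 80.8% | 84 | 83.4% | 90.9% | 90.9% |
| 0.6 | 89.0% | 68 | 91.0% | 95.9% | 94.7% |

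The simpler form Phi[2.80/sqrt(2(1 - rho)) - 1.96] agrees with the first power column to within about one percentage point (80% at rho 0.5, 88% at 0.6).

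**Step 4. Break-even rho.**
- One follow-up: 2(1 - rho) = 1, so 0.50.
- Averaged follow-ups: 1.5(1 - rho) = 1, so 0.33.
- Joint test: 80% power on 2 df needs noncentrality 9.63, so 1 - (7.85/9.63)/1.5 = 0.46.

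**The case against.** The strongest reply is that the article does not state the contrast. Its GEE sentence is one line, and a fuller plan may specify the model. A model that keeps T0 as a response but constrains the arms to be equal there also fits the abstract, and it loses nothing. This stands: difference in change is the natural reading, not a quotation. The Missing data analysis section, which speaks of comparing final results by allocated arm, points rather to a follow-up comparison. That is a further reason to state which is meant.

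A second reply is that the planned covariate adjustment may include the T0 score. This does not rescue the unconstrained model. A respondent-level main effect shifts all of that respondent's visits equally and cancels from the arm-by-time contrast while T0 remains a response.

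A third reply is that rho may well exceed 0.5, since T0 and T1 use the same questionnaire shortly before and after the session. That is possible. At rho 0.6 a change contrast beats a follow-up-only comparison, though it still trails the adjusted one (89.0% against 94.7% for one follow-up).

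A reader might infer more: that the stated 80% is lost unless rho reaches 0.5, and secured if it does. The documents support neither half. The threshold of 0.5 belongs to change to a single follow-up only. And the 80% was computed for proportions, while the GEE is described for scores with no SD or mean difference given, so no value of rho makes it the power of the score analysis. The figures above also set aside the small number of districts (six). Nor is a change contrast invalid: under randomisation it is unbiased in expectation, and the issue is precision.

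**Conclusion.** The point holds as one of precision and of mismatch between analysis and sample size. As worded, the plan most naturally compares change between arms. For one follow-up that has a larger variance than baseline adjustment at every rho below 1; the adjusted variance is 20% to 40% smaller for rho from 0.6 down to 0.2. It is also not the comparison used to obtain 84.

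Taken at face value, the sample size gives a one-follow-up change contrast about 60% power at rho 0.2, 66% at 0.3, about 80% at 0.5 and 88-89% at 0.6. These figures rest on an assumed rho, equal variances, no clustering beyond the plan's own design effect, and the reading of the GEE sentence as an unconstrained arm-by-time contrast. They show the relative cost of the contrast; they are not the trial's true power for the scores.

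**What to change.** In the abstract's Method paragraph and the GEE section, state that the GEE response is the T1 and T2 scores, with arm, visit, arm-by-visit and the respondent's own T0 score on the same outcome as a covariate. Alternatively, keep T0 as a response and constrain the arm means to be equal there. Define the treatment effect as the adjusted between-arm difference at follow-up, and label within-arm change as descriptive.

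In Sample size estimation, state that the 80% refers to a between-arm comparison of follow-up proportions.

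The cost is wording only: no new visits, data or respondents, and no change in N for this point. There is one extra coefficient per model, and missing T0 scores have to go into the multiple imputation already planned.

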### Study design and study location

This study is a two-armed, parallel, single-blinded, cluster-randomized trial. The cluster in this study is defined as a district in Selangor. There are two groups which are the intervention group and the control group. Both groups follow a similar design until the end of the study. The clusters and participants are blinded for the study. The intervention group will receive HEBI, while the control group will receive a non-communicable health program.

Selangor is one of 13 states in Malaysia, located on the west coast of the Malaysian Peninsular. Selangor covers 7930 km2 [8], with a total population of 6.47 million reports to the Department of Information Malaysia, ranking it the most populous state in Malaysia (19.9%). It has a population growth rate, 1.4% and a high level of urbanization (91.4%) [8]. In addition, it has the largest economy in Malaysia in terms of gross domestic product (GDP) contribution, contributing 22.4% of the total Malaysian GDP [8]. The ethnic composition consists of Malay, 52.9%, Chinese, 27.8%, Indian, 13.3%, and other ethnic groups.

The study will carry out in six districts in Selangor state. First, those districts are chosen based on similar backgrounds related to the flood disaster. Then, those districts are ranked based on floods every year and the severity of the disaster using the Department of Irrigation and Drainage Malaysia data. Based on the rank, district Hulu Langat, Hulu Selangor, Kuala Selangor, Sepang, Sabak Bernam and Gombak were included in this study. Then those districts are divided into intervention groups and control groups using a coin toss. As for respondents, they were selected from each household in those districts based on eligibility.

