### Sampling method and subject recruitment

Randomization of the participants will conduct based on the district they belong to. The six districts chosen earlier were randomly assigned into the intervention and control groups with 1:1 allocation. Thus, three districts belong to the intervention group, and three are used in the control group. Figure 2 shows the procedures involved in the recruitment of subjects in this study.

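### Districts are randomised three against three, but the GEE is described for repeated measures on respondents only, and no analysis section accounts for the district

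*Protocol article*

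**What the plan says.** Study design and study location: "The cluster in this study is defined as a district in Selangor". Sampling method and subject recruitment: "The six districts chosen earlier were randomly assigned into the intervention and control groups with 1:1 allocation", so that "three districts belong to the intervention group, and three are used in the control group".

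Sample size estimation allows for clustering once, through a design effect with an average cluster size of 31 and an ICC of 0.005. That ICC is described as adjusted for individual-level and cluster-level characteristics.

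The Abstract (Method) ties the GEE to longitudinal correlated scores at the three visits. Data entry and analysis has the data put in long form for the GEE. The GEE section presents the data as repeated measures and says of the comparison: "between and within treatment groups over time points when adjusting for covariates, the Generalized Estimating Equation (GEE) will be used". The significance rule is given under Data entry and analysis: "A significant alpha level of 0.05 will be used for inferential analysis", and P-"values will be stated as two-sided".

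None of these sections makes the district the GEE subject, a random or fixed effect, or a covariate. None gives a correction for having only six clusters.

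**The concern.** Repeated measures on one respondent are one source of correlation. Respondents sharing a district are another, and it is the second that governs the precision of a comparison between randomised districts. A GEE whose only correlated unit is the respondent treats 84 people as 84 independent pieces of evidence about the arm effect, when only six units were allocated. Its standard error for the between-arm difference is then too small, and an ineffective module is declared effective more often than the stated 5%.

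The Intervention section gives reason to expect similarity within a district: group talks, field visits and revision of community-level emergency plans are shared experiences. The sample size section recognises clustering, so the analysis is out of step with the design and with the protocol's own calculation.

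**Working it through.** **Inputs from the protocol.** Six districts, 3 v 3; two-sided alpha 0.05; z = 0.842 for 80% power; proportions 0.79 and 0.40; ICC 0.005; cluster size 31; attrition 34%; final total 84. The planned total implies 84/6 = 14 per district at entry and 55.2/6 = 9.2 after attrition. **Assumed:** ICCs of 0.05 and 0.10, shown as a range.

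**1. The protocol's own figure.** [1.96√(2×0.59×0.41) + 0.842√(0.79×0.21 + 0.40×0.60)]² = 3.61, and 3.61/0.1521 = 23.7, so 24 per group. (The printed numerator is 3.53; n is unchanged.) Then 48 × [1 + 30×0.005] = 55.2, and 55.2/0.66 = 83.6, so 84. The sample size reproduces.

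**2. District ignored, comparison at one time point.** With DE = 1 + (m−1)×ICC, the true error of a nominal 5% test is 2×[1 − Φ(1.96/√DE)].

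| m per district | ICC 0.005 (protocol) | ICC 0.05 (assumed) | ICC 0.10 (assumed) |
|---|---|---|---|
| 9.2 | DE 1.041: 5.5% | DE 1.41: 9.9% | DE 1.82: 14.6% |
| 14 | DE 1.065: 5.8% | DE 1.65: 12.7% | DE 2.30: 19.6% |
| 31 | DE 1.15: 6.8% | DE 2.50: 21.5% | DE 4.00: 32.7% |

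The last row uses the cluster size from the design effect, which is not the number the planned total delivers.

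Simulation of a respondent-level sandwich analysis (10,000 trials per setting, 14 per district) gave 6.8%, 14.2% and 21.1%. These are slightly above the formula; the same analysis gave 5.2% at ICC 0.

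**3. Group-by-time contrast.** A district effect that is constant over time cancels from a change score. In simulations with 14 per district, the error then stayed at about 5–6% for ICCs from 0.005 to 0.10. With half the district variance varying over time and a within-person correlation of 0.5, it was 6.2%, 14.1% and 21.2% at ICC 0.005, 0.05 and 0.10.

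**4. District as GEE subject, uncorrected.** With k = 3 equal clusters per arm, the sandwich variance divides by k² = 9 where the unbiased form divides by k(k−1) = 6. So z = t₄ × √1.5, and P(|t₄| > 1.96/1.2247) = 18.5%. The ICC does not enter. Simulation gave 18–19%.

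**5. District means, t-test on 4 df.** Simulated error was 4.6–5.4% in every setting.

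**6. Power of that test at 0.79 v 0.40.** The standard error is √[(0.1659 + 0.24)×DE/(3m)].
- 14 per district, ICC 0.005: SE 0.101, non-centrality 3.84, power about 82%.
- 9.2 per district, ICC 0.005: SE 0.124, non-centrality 3.15, power about 66%.
- 9.2 per district, ICC 0.10 (assumed): power about 44%.

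**7. Permutation test.** Six districts taken three at a time give 20 allocations, so the smallest two-sided p is 2/20 = 0.10.

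**The case against.** The GEE section is two sentences in a condensed article. It names no subject variable, working correlation or variance estimator, and a full protocol or analysis plan may supply them. Calling the data repeated measures explains why GEE was chosen; it does not say that clustering was ruled out, and the design effect shows the authors knew of it. This is a fair limit: the documents do not show that the district will be left out of the fitted model. What remains is that the article does say which correlation its main model addresses, and that level is not sufficient for the randomised comparison. This is more than an omitted detail.

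The size is also open to challenge. At the only ICC the protocol gives, the excess is small. A reader might infer that the plan's 5% test really runs at 20%. The documents do not support that, because the figure needs an ICC twenty times the stated one. A value above 0.005 is possible, since 0.005 is a covariate-adjusted figure from a cited source, but it remains an assumption. Nor is 18.5% the error rate of the stated plan: it belongs to an analysis the protocol does not describe, and serves only as a warning about the obvious repair.

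The wording about change over time points suggests a group-by-time contrast, where constant district differences cancel. That narrows the claim. It does not remove it, because delivery district by district and local events between visits can make district effects change over time.

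Finally, a reader might count the baseline tests ("The chi-square test will be used for categorical data, while the independent T-test or Mann-Whitney U test will be used for continuous data") and the normality fallback ("otherwise, non-parametric equivalents will be used") as part of the same fault. They also treat respondents as independent. But the baseline tests describe comparability and do not alter the error rate of the treatment test, and the fallback is general wording not tied to the GEE. The point does not rest on either.

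**Conclusion.** The concern holds in this form: the analysis text provides for repeated measures only, while the design and sample size sections make the district the randomised and correlated unit. For a between-arm test at a time point, the consequence is a type I error of about 5.5–7% at the protocol's ICC (9 to 31 per district), and about 10–20% if the ICC were 0.05–0.10 (9 to 14 per district). The first range rests on protocol figures; the second rests on assumed ICCs. Both assume equal district sizes. For a group-by-time contrast, the excess depends on how far district effects vary over time, which the protocol does not quantify.

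The inflation at the stated ICC is modest, but the wording needs correcting, because the between-arm comparison is the trial's main inference and the simplest repair, making the district the GEE subject without a small-sample correction, would give about 18.5%.

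**What to change.** In the GEE section, state that the primary between-arm comparison is made at district level: district means of the T2 score, adjusted for the T0 score, compared three against three by a t-test on 4 df. GEE can stay for describing change within an arm.

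An alternative is a model with a district level, a small-sample correction and the degrees of freedom held at the between-district value of 4. The df should be fixed in advance. At ICC 0.005, a moment estimate of the district variance was zero or negative in about 55% of simulated trials, and a mixed model left to estimate it can slip back to respondent-level inference. It is therefore not interchangeable with the 4-df test unless the df are constrained.

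Do not rely on a rank or permutation test of the six districts, which cannot reach 0.05.

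The cost goes beyond wording. The critical value rises from 1.96 to 2.78, so intervals are about 1.42 times as wide (2.78/1.96) for the same standard error. Power for 0.79 v 0.40 at ICC 0.005 is about 82% with 14 per district, but about 66% once 34% are lost. The 80% in Sample size estimation should be restated for this analysis, and the number of respondents or districts reconsidered if 80% is still the aim.
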